## 2. Materials and Methods

### 2.1. Study Design and Setting

This will be a prospective, nonrandomized trial with patients with scoliosis. All subjects with severe scoliosis will be recruited from the outpatient clinic of the orthopedic department of the University Hospital Frankfurt. In addition to routine projection radiographs and preoperative CT scans that are available in some cases and/or X-ray EOS scans, special 3D thin-slice MRI sequences will be retrospectively reformatted during the required preoperative MRI scan for all study participants, as well as a three-dimensional back scan and an intraoral scan. All procedures and scoliosis parameters obtained will be compared and correlated.

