### 2.2. Participants/Study Subjects/Sample Size Calculation

The sample size calculation will be based on our primary hypothesis. To evaluate whether thin-slice MRI examination with reconstruction can adequately address the relevant questions for preoperative planning instead of CT, we will determine the Wanatabe classification for pedicle type based on both MRI and CT data and calculate Cohen’s kappa. Our goal is to demonstrate a Cohen’s kappa of more than 0.4 (indicating at least moderate agreement according to standard classification) using a one-sided test with a significance level of alpha = 5%. For sample size planning, we will simplify our assumptions by considering that the categories are approximately equally populated and that there is, in fact, at least substantial agreement with a kappa of 0.75. In this scenario, at least 30 patients will be sufficient to achieve a statistical power of 95%, even with a 5% drop-out rate. A relatively high power was chosen to account for an uneven distribution and to ensure sufficient statistical power overall. For the correlation tests involving quantitative measures of the secondary objectives, we also expect adequate statistical power. In general, statistical tests will be conducted with a two-sided approach and a significance level of alpha = 5%, except for the primary objective.

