Within the framework of the project, at least 50 male and female children and adolescents aged > 7 to 18 years will be analyzed (according to the calculated power analysis). All of them will present to the Orthopaedic Clinic of the University Hospital Frankfurt with a clinical picture of scoliosis between 2022 and 2025. Height and weight will be recorded at admission. In addition, a separate medical history form will be used to record any previous conservative therapies (orthotics, braces, physiotherapy), including the type and duration of treatment. The following criteria apply for inclusion in this study:-Children/adolescents diagnosed with severe scoliosis by major curve in the X-ray > 40° [36];-Planned MRI examination of the spine at the Institute of Neuroradiology;-An EOS and/or a CT examination of the spine has already been performed as part of the diagnosis or must still be planned independent of the present project;-Children must be able to cooperate (>7 years, no motor or cognitive impairment);-Consent of the legal guardians as well as of the child.-The following criteria apply for exclusion from this study:-There will be no upper curve limit as an exclusion criterion;-Previous spinal surgery;-Mental and/or physical impairments that do not warrant a 30 min MRI scan or contraindications to an MRI scan (i.e., implants, pregnancy).

Informed consent from a parent and/or legal guardian for study participation will be obtained.

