### 2.3. Measurement Protocol

Routine diagnostics: Following the initial scoliosis diagnosis, which will include X-rays in two planes, additional routine standardized examinations with functional images and, if necessary, 3D imaging using EOS X-rays of the spine and/or if deemed necessary a preoperative CT of the spinal axis will also follow within this study (Figure 2). The indication for MRI examination to exclude congenital malformations will be a precondition for this study (Figure 2).

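### The 95% power stated for the primary MRI-versus-CT kappa holds only for patients who have both scans; CT is not required at entry and the size is given as both 30 and 50, so that power is not secured.

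*Protocol article*

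**What the plan says.** All references are to the protocol article.

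- **Primary comparison (section 2.2):** "we will determine the Wanatabe classification for pedicle type based on both MRI and CT data and calculate Cohen’s kappa". The target is set as "Our goal is to demonstrate a Cohen’s kappa of more than 0.4", "using a one-sided test with a significance level of alpha = 5"%. The statistical analysis paragraphs at the end of section 2.3 repeat this as the main test.
- **Power statement (section 2.2):** "at least 30 patients will be sufficient to achieve a statistical power of 95%, even with a 5% drop-out rate". The planning assumptions are a true kappa of 0.75 and roughly equal categories. The power was set high to leave room for uneven categories.
- **Second size (section 2.2, next paragraph):** at least 50 children and adolescents "will be analyzed (according to the calculated power analysis").
- **Availability of CT (section 2.1):** "preoperative CT scans that are available in some cases and/or X-ray EOS scans". The thin-slice MRI, by contrast, is for every participant.
- **Entry criterion (section 2.2):** "An EOS and/or a CT examination of the spine has already been performed as part of the diagnosis or must still be planned", independently of the project.
- **CT during the study (section 2.3):** "if deemed necessary a preoperative CT of the spinal axis will also follow within this study".

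**The concern.** The power statement counts patients, but the statistic needs pairs. A child who enters with EOS and never has a CT contributes nothing to the primary kappa. The only loss the calculation allows for is 5% drop-out. Missing CT is a separate loss, and by the article's own description it will occur.

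The two sizes add to the difficulty. The only power analysis shown ends at 30, yet 50 is credited to it. Neither number is described as a count of patients with both scans, and no minimum number of CTs is set. Recruitment could therefore meet either target while the primary analysis has fewer pairs than the stated power needs.

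The stake is the main claim. The Results section sets out the goal of doing away with preoperative CT, and only patients with both scans can support that.

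**Working it through.** **Inputs from the article**
- Null kappa 0.40, planning kappa 0.75, one-sided alpha 5%, power 95%, drop-out 5%, roughly equal categories (section 2.2).
- Four categories, A to D (Table 1).

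**Assumptions, because the article does not give them**
- One rating per patient.
- The share of enrolled patients who have a CT, taken from 20% to 100%.

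**Step 1: variance.** With four equal categories, chance agreement is 0.25. Observed agreement is kappa × 0.75 + 0.25, which is 0.55 at kappa 0.40 and 0.8125 at kappa 0.75. The large-sample variance per pair is po(1 − po)/(1 − pe)²:
- null: 0.55 × 0.45 / 0.75² = 0.440, SD 0.663
- alternative: 0.8125 × 0.1875 / 0.75² = 0.271, SD 0.520

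**Step 2: reproduce the plan's 30.** n = [1.645 × (0.663 + 0.520) / 0.35]² = 30.9, so 31 evaluable pairs, or 33 after allowing for 5% loss (31/0.95 = 32.6). With the alternative variance only, the result is 24 pairs, or 26 after loss. The stated 30 lies between 26 and 33, so it is reproduced, provided it counts patients with both scans.

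**Step 3: power for n pairs.** Power = Φ[(0.35√n − 1.645 × 0.663)/0.520]. At n = 28 this is 0.93, at 30 it is 0.94 and at 31 it is 0.95. Simulation gave 0.932 at 28 and 0.945 at 30. At 47 to 50 pairs it is about 0.99, so 50 is not what the stated 95% calculation produces.

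**Step 4: effect of the CT share, 50 enrolled and 5% lost (47.5 remain)**

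| Assumed CT share | Pairs | Power, both variances | Power, alternative variance only |
|---|---|---|---|
| 20% | 9.5 | 0.49 (0.47 at 9 pairs) | 0.67 |
| 40% | 19 | 0.80 | 0.90 |
| 50% | 23.75 | 0.88 | 0.95 |
| 60% | 28.5 | 0.93 | 0.97 |
| 70% | 33.25 | 0.96 | 0.99 |
| 100% | 47.5 | 0.99 | >0.99 |

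By the formula with both variances, 95% power needs a share of 33/50 = 66%. With the alternative variance only, about 24/47.5 = 51% is enough.

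**Step 5: if only 30 are enrolled, 5% lost.** Shares of 30%, 50%, 70% and 100% give 0.45, 0.67, 0.82 and 0.93 (both variances).

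**Step 6: uneven categories.** With an assumed 60/20/10/10 split, about 42 pairs are needed for 95%, and 25 pairs give 0.78. The article already assigns its high power to this purpose, so the same margin cannot also be counted on to cover missing CT.

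**The case against.** Several points on the other side have weight.

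*One rating per patient is not stated.* Table 1 refers to pedicles in the plural, so a patient may supply several paired ratings. As an illustration, assume 10 pedicles per patient and a within-patient correlation of 0.5. The design effect is 1 + 9 × 0.5 = 5.5, so 19 CT patients give an effective 190/5.5 ≈ 35 pairs and power of about 0.97; 14 give about 0.90 and 9 about 0.73. This stands as a limit on the figures above. It does not answer the point, because section 2.2 counts patients and a patient without CT supplies no pair at all. The normal approximation is also rough at the smallest counts.

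*The CT share may be high.* The Introduction says pedicle thickness has mainly been assessed by CT, section 1.1 calls preoperative CT routine, and the cohort has curves above 40°. That is fair. Against it, section 2.1 limits CT to some patients and the Discussion leaves imaging to the surgeon. A reader might infer that the primary test will be badly underpowered; the documents do not support that, since they give no share and a high one would preserve the power.

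*The 30 can be read as pairs and the 50 as the whole project, with its back-scan and dental aims.* Both are minimums, and 50 satisfies 30. This is a reasonable reading, and enrolling 50 lowers the risk. But the text credits 50 to the power analysis and does not say that it was chosen to yield 30 pairs.

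*Selection.* A reader might also infer that a kappa from patients in whom CT was thought necessary answers the wrong question. That goes too far: they are close to the population in whom replacing CT matters. It remains true that the result describes those patients and not every preoperative patient.

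**Conclusion.** The point holds as a defect in what is stated. The calculation behind 30 is acceptable, but it applies to patients with both MRI and CT. The entry criteria do not ensure that number, and the 50 does not follow from the analysis it is credited to. The 95% power is therefore not secured, which is a weaker statement than saying it is lost.

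The size depends on an unknown CT share. On the assumptions above, power with 50 enrolled runs from about one half at a 20% share to 0.99 when all have CT, and reaches 95% at a share between about 51% and 66% depending on the variance used. Several ratings per patient would raise these figures; uneven categories would lower them. Severity: should-fix.

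**What to change.** 1. State the primary sample size in section 2.2 as evaluable MRI-CT pairs, with the unit of rating (patient or pedicle) named.
2. Either correct the statement that 50 follows from the power analysis, or show how 50 enrolled yields the required pairs through an expected CT share and the 5% loss.
3. Restate the power for the number of pairs expected. No CT should be requested for the study; the entry criterion already keeps such imaging independent of the project.
4. Limit the primary conclusion to patients in whom a CT was obtained.

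The cost is a few sentences and an estimate of the CT share. The stated power may come out lower than 95%. No extra imaging is needed. A comparison of patients with and without CT would help readers, but that is detail for the analysis plan.

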### 2.2. Participants/Study Subjects/Sample Size Calculation

The sample size calculation will be based on our primary hypothesis. To evaluate whether thin-slice MRI examination with reconstruction can adequately address the relevant questions for preoperative planning instead of CT, we will determine the Wanatabe classification for pedicle type based on both MRI and CT data and calculate Cohen’s kappa. Our goal is to demonstrate a Cohen’s kappa of more than 0.4 (indicating at least moderate agreement according to standard classification) using a one-sided test with a significance level of alpha = 5%. For sample size planning, we will simplify our assumptions by considering that the categories are approximately equally populated and that there is, in fact, at least substantial agreement with a kappa of 0.75. In this scenario, at least 30 patients will be sufficient to achieve a statistical power of 95%, even with a 5% drop-out rate. A relatively high power was chosen to account for an uneven distribution and to ensure sufficient statistical power overall. For the correlation tests involving quantitative measures of the secondary objectives, we also expect adequate statistical power. In general, statistical tests will be conducted with a two-sided approach and a significance level of alpha = 5%, except for the primary objective.

Within the framework of the project, at least 50 male and female children and adolescents aged > 7 to 18 years will be analyzed (according to the calculated power analysis). All of them will present to the Orthopaedic Clinic of the University Hospital Frankfurt with a clinical picture of scoliosis between 2022 and 2025. Height and weight will be recorded at admission. In addition, a separate medical history form will be used to record any previous conservative therapies (orthotics, braces, physiotherapy), including the type and duration of treatment. The following criteria apply for inclusion in this study:-Children/adolescents diagnosed with severe scoliosis by major curve in the X-ray > 40° [36];-Planned MRI examination of the spine at the Institute of Neuroradiology;-An EOS and/or a CT examination of the spine has already been performed as part of the diagnosis or must still be planned independent of the present project;-Children must be able to cooperate (>7 years, no motor or cognitive impairment);-Consent of the legal guardians as well as of the child.-The following criteria apply for exclusion from this study:-There will be no upper curve limit as an exclusion criterion;-Previous spinal surgery;-Mental and/or physical impairments that do not warrant a 30 min MRI scan or contraindications to an MRI scan (i.e., implants, pregnancy).

Informed consent from a parent and/or legal guardian for study participation will be obtained.

The collected data will be stored in a pseudonymized format, in accordance with the local data security policy and in full compliance with GDPR. A specific data protection plan, overseen by the clinic’s data protection officer, will be implemented. The data will be stored in secure, segregated folders, with access restricted to authorized personnel only (e.g., the principal investigator, study physicians, and examiners), who will have the ability to link the data to individual patients through the pseudonymization list. Data from the study will be made available in future publications in anonymized form, in compliance with ethical guidelines, and upon request, according to journal policies and legal requirements. Only the principal investigator, study physicians, and examiners will be able to link the collected data to specific names/patients using a written list. A study folder will be created for each patient, containing the score sheets, which will be securely stored in the senior physician’s office. The transfer of any personal data to other individuals is not planned. All data will be retained for 30 years.

This study was approved by the medical ethics board for research involving human subjects of the Goethe University (2022-611) in Frankfurt am Main, Germany.

X-ray: X-ray images are used to determine the extent of the scoliosis by measuring the Cobb angles Philipps GmbH (Hamburg, Germany). Two straight lines are drawn at the base and top plates that are tilted the most relative to each other. The angle created at the point of intersection corresponds to the Cobb angle. The two vertebrae are called end vertebrae. At the center of the curvature, the vertebra with the maximum rotation is defined as the apical vertebra or apex. If there is also an opposing curvature corresponding to a smaller secondary curvature, this Cobb angle is determined analogously. In addition, the iliac crests should be visualized in the radiograph [1]. This is used to assess the ilium apophysis and thus to determine Risser’s sign. The lateral to medial ossification of the apophysis is determined and divided into different stages [37]. Yang et al. [38] demonstrated strong intraobserver variability. To correctly classify Risser’s sign and prevent errors, they developed a modified staging system [38]. A more reliable method of assessing the remaining growth potential of the spine is the Sanders hand classification. The intra- and interobserver reliability of Sanders and its predictive value in the progression of scoliosis make it a very valuable tool in assessing spinal growth [39].

The most important classification in surgical planning of scoliosis performed on the basis of radiographs (sagittal and coronal) is the Lenke classification [1,12]. The Lenke classification is a system used to classify and describe the types of scoliosis curves seen in adolescent idiopathic scoliosis (AIS). The Lenke classification system divides AIS into three categories based on the location of the curve in the spine: thoracic curves (T) located from the 1st to the 11th thoracic vertebrae; thoracolumbar curves (TL), located in the middle of the spine, from the 12th thoracic vertebra to the 1st lumbar vertebra; lumbar curves (L), located from the 2nd to the 5th lumbar vertebrae. The Lenke classification system is used by spine surgeons and orthopedic specialists to help guide treatment decisions for AIS. Treatment options may include bracing, spinal fusion surgery, or observation depending on the severity of the curve and the age of the patient. The Lenke classification system helps physicians to determine the appropriate treatment plan based on the specific characteristics of the curve. In addition, functional radiographs can be taken according to bending [40]. These are taken in maximum lateral bending to the right and to the left in order to estimate the flexibility of the spine and the potential maximum possible correction [41,42]. Also, on the basis of these radiographs, the primary curvature can be differentiated from the secondary curvature in the case of several approximately equal Cobb angles. 

EOS: The EOS system EOS Imaging (Paris, France) is a medical imaging technology developed by EOS imaging. The system uses a proprietary technology called slot-scanning, which involves capturing two simultaneous X-ray images from different directions as a patient stands or sits in an upright position. This technique provides high-quality, low-dose 2D and 3D images of the skeletal system, particularly the spine and lower limbs, with less radiation exposure compared to that of traditional CT scans. One of the main advantages of the EOS system is its ability to provide full-body images of patients in an upright position, which can be particularly useful for assessing conditions such as scoliosis or assessing the alignment of lower limb joints. The system also provides high-resolution images, which can aid in the diagnosis and treatment planning of orthopedic conditions [43].

MRI: The MRI device used will be a 1.5 Tesla device (Ingenia) from Philipps GmbH (Hamburg, Germany). The sequences to be used consist of an axial and a sagittal T2w, a coronary stir, a sagittal T1w, and an axial T1w with and without fat saturation, if applicable. Furthermore, an isovoxel 3D T2 sequence, with 1 mm slices, will be reformatted in all spatial directions following the examination. 

Radiation-free back scanner: The three-dimensional back scanner “BodyMapper” (ABW GmbH, Frickenhausen, Germany) records changes in the upper back posture while standing by using video-raster stereography. The sampling frequency is 50 Hz with a spatial resolution of 1/100 mm. Marking of six anatomical fixed points on the bare back is required to generate the evaluation parameters. These anatomical landmarks are shown in Figure 1. In comparison with other methods, Asamoah et al. [44] found it to be effective in diagnosing scoliosis and certain deformations. Values for sensitivity and specificity were 98% and 84%. Other authors [45] reported good correlations with angle measurements using video-raster stereography and X-ray (r > 0.8 to 0.93). Regarding evaluation criteria of the upper body posture, all calculated evaluation parameters can be divided into three parts: the spine (marker on C7 and Rima Ani), shoulder (marker at the highest place of the left/right scapula), and pelvis area (marker on left and right spina iliaca posterior superior [SIPS]). Details were already described by Ohlendorf et al. [46].

Intraoral scan: An intraoral scan will be performed using an intraoral scanner (Primescan, Sirona Dentsply, Bensheim, Germany), and the resulting 3 -model will be analyzed using software (OnyxCheph^3TM^ Version 3.2.223 (608), Image Instruments GmbH, Chemnitz, Germany). In all three dimensions (anteroposterior, transverse, and vertical), occlusal conditions, malocclusion, and dental anomalies will be examined, i.e., transverse: crossbite or scissor bite; anteroposterior: overjet and angle classification; vertical: overbite, open bite or deep bite.

### 2.3. Measurement Protocol

Routine diagnostics: Following the initial scoliosis diagnosis, which will include X-rays in two planes, additional routine standardized examinations with functional images and, if necessary, 3D imaging using EOS X-rays of the spine and/or if deemed necessary a preoperative CT of the spinal axis will also follow within this study (Figure 2). The indication for MRI examination to exclude congenital malformations will be a precondition for this study (Figure 2).

Additional protocol: After inclusion in this study, anatomical landmarks will be marked on the patient’s back for all subsequent examinations and visualized using different markers in the corresponding examination modality. EOS image: Additionally, visible markers will be glued to each of the six markers of the back scan using adhesive tape so that the same reference markers will also be available here for evaluation purposes. MRI-image: Liquid-containing capsules will be taped onto the markers of the back scan instead of metal markers during the X-ray. In cases of splitting the measurement over two days, the X-ray image will be taken first. For this purpose, the markers of the back scan will then be marked with a permanent marker so that the same position can be used again the next day for the rest of the measurements. Additional diagnostics: The two additional examinations by means of the back scanner and the oral scanner will take a total of approx. 15 min and will be coordinated with the MRI examination in terms of time and space. All preoperative examinations will be performed at close intervals (within 7 days) to minimize the risk of measurement deviations due to disease progression. Back scan: For this purpose, six anatomical landmarks will be marked on the unclothed back [46]. All patients will stand in habitual body posture at a predefined distance of 90 cm with the back to the scanner. The arms should hang loosely next to the body with the gaze directed straight ahead in order to exclude changes in head posture. One measurement will last 5 s and will be repeated 5 times with short periods of rest in between. Intraoral scan: Immediately before the MRI examination is performed, the dentition will be scanned in addition to the back scan. For this purpose, the subject will sit on a chair with the body upright and the head straight. Postoperative routine diagnostics: In the case of surgery, an X-ray and/or EOS will be performed as standard procedure following surgery at the discretion of the surgeon depending on the clinical course, and, in the case of postoperative complaints, a CT could be performed to demonstrate the screw position. In addition, the anatomical landmarks should be marked with visible markers, and the back scan should be performed again on the day of the postoperative X-ray or EOS examination, taking an additional 5 min for the patient.

Statistical data analysis

